### Outcomes

#### The primary outcomes

Primary care interval is defined as the time from the first presentation of a cancer-relevant symptom in primary care until the date of referral to secondary care for investigation [16]. It was hypothesised that the CME would lower the primary care interval by increasing the GP’s readiness to refer.GP referral rate is defined as the number of patients referred by a specific GP to a cancer fast-track pathway per 1000 patients listed with the GP. The CME was expected to increase the referral rate.

#### The secondary outcomes

GP knowledge is defined as knowledge on *i)* Cancer as a condition with a low prevalence, *ii)* PPVs for cancer of selected symptoms, *iii)* Typical pitfalls and *iii)* Initial cancer presentation. This is measured by requesting the GP to indicate a probability percentage (0-100%) on questions such as; *what is the likelihood of a 50-year-old patient having cancer at the time you choose to refer to a cancer fast-track pathway? What is the likelihood of a patient, smoker, aged 40 and above, having lung cancer the second time the patient presents with haemoptysis in your practice? What is the risk for a lung cancer not being detected on a chest x-ray at the time of diagnosis?* W*hat is the proportion of patients with colorectal cancer who initial presented an alarm symptom*?GP attitude towards early cancer diagnosis, assessed as a score on a 1–5 Likert scale. It is defined as attitude to *i)* Use of fast-track referral, i.e. whether the referral option is considered complicated and/or time-consuming. *ii)* Use of healthcare resources, i.e. whether risk taking is affected by fear of overuse or fear of delayed diagnosis. *iii)* Use of patient resources, i.e. whether risk taking is affected by fear for unnecessary distress or need for necessary investigation to find those with cancer in an early stage.GP self-assessed readiness to refer is defined as the proportion of hypothetical patients referred at their first presentation based on GP responses to patient scenarios (vignettes) concerning cancer diagnosis. 4) GP-assessed risk of cancer for referred patients. 5) Referred patients’ GP visit rates 6 months prior to diagnosis compared with their earlier use of general practice. 6) The proportion of patients with cancer among referred patients for each GP (GP’s PPV for diagnosing cancer when a patient is referred to the cancer fast-track pathway). 7) Cancer patients’ clinical tumour stage at the time of initiating treatment. 8) Cancer patients’ one-year survival measured as the proportion of cancer patients per GP alive one year after the date of diagnosis (Figure 3).

**Figure 3 Fig3:**
[figure not shown]
**The aspects of the interventions that were measured and the outcomes.** The first column depicts the elements in the change process; the second column classifies the corresponding outcomes; the third column describes the methods applied; and the fourth column depicts the data sources.

### Data

Data are collected by GP-completed online questionnaires before and after the CME and by GP-completed one-page forms on each patient referred to cancer investigation within an 8-month period surrounding the CMEs. These data will be expanded with register data.

#### Online questionnaire: Development, pilot testing and data collection

The online questionnaire consisted of vignettes and direct questions. The vignettes were validated and tested in the ICBP module-3 studies [37]. They were developed to describe the likely GP actions which included GP readiness to refer when a patient presented with symptoms suggestive of lung cancer (two vignettes), colorectal cancer (two vignettes) or ovarian cancer (one vignette). GPs were asked to complete two randomly chosen vignettes. Each vignette had two or three phases: phase one represented the first patient presentation; phases two and three represented subsequent visits where the patient’s symptoms had developed; each phase had a defined PPV for cancer.

The direct questions were based on the elements of the CME developed as *ad hoc* questions to measure a possible CME effect on knowledge (6 items) and attitude (13 items). The first version of the questionnaire was developed by the authors and academic GPs in an iterative process that focused on the specific elements for CME intervention. The questionnaire was piloted for cognitive understanding among six doctors and, finally, among 12 GPs. Data quality, missing variables, and ceiling and floor effects were checked, and a revised version of the questionnaire was produced (Additional file 1).

The GPs were allocated a CME date. The invitation to the online questionnaire was sent by e-mail to the GPs 1 month before the CME. Non-responders received a reminder by e-mail after two weeks. A second questionnaire similar to the first one except for two new randomly selected vignettes was sent by e-mail 7 months after the CME to GPs who responded to the first questionnaire. Non-responders were reminded by e-mail after two weeks.

#### One-page forms on referred patients: Development, pilot testing, and data collection

This form was used to collect specific clinical information on patients referred from GPs to the fast-track pathway on cancer suspicion. The one-page form requested the patient’s personal identification number, the date of hospital referral, the date of first presentation of symptoms in general practice related to cancer suspicion, the symptoms presented at the time of referral, the specific fast-track pathway, and the GP’s assessment of the patient’s risk of cancer. GPs were asked to rate a specific risk for cancer by indicating a probability percentage (0–100) (Additional file 2).

All the items mentioned above have previously been validated in studies performed by the Research Unit [15,44]. The form was piloted in three steps. Seven GP trainees were observed while they filled in the form about the most recent patient they had referred on cancer suspicion. They were interviewed about any problems encountered and how they understood the items. Three GPs then completed forms in their daily practice over a 2-week period in order to check its feasibility. Finally, 21 GPs were asked to fill out and subsequently send the forms electronically to the Research Unit to verify the feasibility of the electronic transfer and the optical scanning of the forms [51].

In August 2012, all GPs in the Central Denmark Region received a pad with 25 forms. They were requested to complete a form each time they referred a patient to a cancer fast-track pathway within an 8-month period (September 2012-May 2013). Patients referred to fast track were also identified in a regional database (PAS) and in a radiological database (breast cancer). If the GP form was missing, the GP was sent a form for the particular patient and kindly requested to complete it. This form was extended with an item on the patient’s route into a fast-track pathway investigation to include only patients referred from GPs on cancer suspicion (Additional file 3).

The one-page form was designed and processed in the computer programme Teleform Enterprise Version 8.0 (Cardiff software Inc., San Marcos, CA, USA). Handwritten data including presenting symptoms were coded by the first author ([name]) before scanning [51].

All data will be transferred to the statistical program Stata (Stata software, version 11.1, StataCorp, College Station, Tex, USA) and will be checked for errors. If errors are encountered, the original form of the completed questionnaire will be inspected, and the database entry will be corrected.

#### Incentives

Remuneration was 33 Euros for completing the first online questionnaire and 17 Euros for completing the second online questionnaire. The GPs received 100 Euros for completion of forms on referred patients during the 8-month period.

#### Register data

Each inhabitant with a permanent residence in Denmark has a 10-digit personal identification number, the CPR number. This number is registered in the Danish Civil Registration System and allows linkage between all national registries at the individual level. A cancer patient’s vital status will be obtained 12 months after the date of diagnosis.

The provider number registry contains the names and addresses of every Danish GP, the number of GPs in each general practice, and patient list size including the patients’ sex and age.

The Primary Care Referral Registry (an online database) stores copies of all electronic referral letters sent from general practice to hospital. We will develop an algorithm to identify patients referred on cancer suspicion in the 8-month study period to increase the completeness of the data on referred patients.

The Danish National Patient Registry [52] will be used to obtain information about comorbidity and cancer diagnoses.

The Danish National Health Service Registry [53] will be used to count the number of contacts of referred patients to general practice during the 6 months preceding the referral date. Each patients previous use of general practice patient will be counted and serve as a basis for comparison.

The Danish Cancer Registry [54] will be used to identify patients with cancer among all referred patients. From this registry, we will also obtain data on date of diagnosis, cancer type and tumour stage.

Statistics Denmark [55] holds data stored in the Integrated Database for Labour Market Research. These data will be used to calculate a deprivation score for each general practice (Table 3).

**Table 3 Tab3:** **Detailed description of registers used for data collection to investigate the effect of the CME**

**Name of register**	**Description of registers**
The CPR number and the Danish Civil Registration System (CRS)	In Denmark (and other Nordic countries), researchers have exceptional opportunities to perform register-based research because every person with a permanent residence in Denmark has a unique personal identification number. At birth or immigration, all citizens in Denmark are allocated a personal ten-digit identification number, the CPR number. This number is registered in the Danish Civil Registration System (CRS) and allows linkage between all national registries at the individual level. The CRS contains information about vital status (dead or alive) and residence.
The Primary Care Referral Registry	An online shared database with all electronic referral letters sent from general practice clinics to hospitals. Contains information about sender, receiver and patient including anamnesis. We will develop an algorithm to identify patients referred for cancer investigation.
The Danish National Patient Registry(NPR) comprises The Patient Administrative System (PAS)	The NPR is a national database unifying information from the five regional Patient Administrative System (PAS). The NPR is run by the National Board of Health who carries out ongoing validation of the data from PAS. Both the NPR and PAS are continuously updated. They comprise variables like the patient CPR number, dates of admission and discharge, diagnoses classified according to the International Classification of Diseases (ICD-10) (Comorbidity), codes for undertaken procedures, the GP’s provider number and different additional codes. Of particular relevance for this study, we identified patients referred to fast-track cancer pathways by the additional code DZO31 in PAS every second week.
List of patients referred to fast-track pathway for breast cancer from four radiological departments	Since patients referred to the fast-track pathway for breast cancer are not registered with a DZO31 code, like other investigations in fast-track pathways, an additional data list was periodically received from the four radiological departments in Central Denmark Region.
The Danish Cancer Registry (DCR)	The DCR has been recording primary cases of cancer on a nationwide basis since 1943 and has been shown to be accurate and to have a nearly complete registration of cancer cases. The files of the DCR provide information on cancer type, site morphology and history of cancer. Tumours in the registry are coded according to the ICD-10 (seventh revision before 2004), which includes a four-digit code for tumour morphology. If a person develops more than one primary tumour, each tumour is generally registered and counted as an individual record. We used the DCR to find prior and incident cancer diagnoses among referred patients and to obtain information on date of diagnosis and tumour stage.
Danish National Health Service Registry (NHSR)	The NHSR for primary care is a national register of all health professionals contracted with the tax-funded health-care system, e.g. GPs. The register is run by the National Board of Health, and its data are based on the health professionals’ invoices to the regional health administrations. Among others, the NHSR holds information on name and addresses of every provider number. A provider number may refer to several providers if, for example, several GPs form a medical practice partnership.
Patient list	List of patients connected to each provider number. The list contains information on patients’ CPR number, including age and sex.
The provider number and the Provider Number Registry	Every health professional contracted with the tax-funded health-care system has a provider number. The provider number system is used to control the supply of GPs and, to a certain extent, to control expenditures. GPs are allowed to sell or share their provider number and office facilities. GPs can choose to work in solo practices or in group practices (in the latter case, the GPs can share a provider number or have one provider number per GP). Danish citizens are free to choose their own GP unless the GP list is closed (GPs are allowed to close their lists when the number of persons on the list reaches 1,600 persons). The list system enables the GP to develop a better knowledge of the individual patient which ensures continuity of care. The Provider Number Registry contains information on the name and addresses of every health professional with a provider number.
Statistics Denmark	As a central authority, Statistics Denmark is responsible for collecting, processing and publishing statistical information and for making statistical analyses and prognoses. Researchers can apply for data from Statistics Denmark for further analysis. We will use data from the Integrated Database for Labour Market Research which is owned by Statistics Denmark to calculate a deprivation score for each GP’s practice population. This Danish deprivation index (DADI) has eight variables that are scored individually and sum up to a score between 10 and 100; the higher the number, the greater the extent of deprivation in the practice population. The variables used are (i) proportion of adults aged 20–59 with no employment, (ii) proportion of adults aged 25–59 with no professional education, (iii) proportion of adults aged 25–59 with low income, (iv) proportion of adults aged 18–59 receiving public welfare payments (transfer income or social benefits), (v) proportion of children from parents with no education and no professional skills, (vi) proportion of immigrants, (vii) proportion of adults aged 30+ living alone and (viii) proportion of adults aged 70+ with low income (= the lowest national quartile).

### Statistical analyses

For the descriptive part, differences will be tested using appropriate parametric and nonparametric statistics. The effect of the intervention will be analysed in a generalised, linear, random-effects model with random effect of GPs. The data will be used to assess whether further modelling of inter-correlation within practice and within clusters is required, and whether the intervention effects are equal for all GPs or in random interaction with them. Analyses will be performed both in the full GP population “intention to intervene” (cluster level) and in the three GP subgroups: 1) GPs who participated in the CME, 2) GPs who did not participate in the CME, but had at least one colleague who participated, and 3) GPs who did not participate in the CME and who had no colleagues who participated. A colleague is defined as a GP with the same clinic address as the respondent. The intervention effect on GP knowledge and attitude will be measured in a before-after analysis.

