## Method

### The CME intervention

#### Setting

The study was performed in one of the five Danish Regions (Central Denmark Region) which has 1.27 million inhabitants and 417 GP clinics with 836 GPs. In Denmark, GPs own their private clinics and are on a contract with the Danish Regions on a central, negotiated scheme [33]. Part of this scheme includes remuneration for participation in CME. As a first line in the Danish healthcare system, the GPs provide free access to medical advice and act as gatekeepers to hospital and private specialists. Each citizen (99%) is listed with a specific general practice clinic.

The regional CME on early cancer diagnosis was initiated by a team comprising researchers, a regional academic coordinator, hospital-GP liaison advisors, a CME supervisor and three leading hospital consultants. A working group was established to operationalise the CME. This group counted four academic GPs of whom two were hospital-GP liaison advisors, one CME supervisor and one researcher ([name]). A research group (the authors) identified the barriers as described below. The Danish government funded the CME.

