#### Power calculation

Power calculation is based on the primary outcome: Primary care interval. The sample size is calculated to detect a reduction in the longest primary care intervals >20 days [56] from 25% to 20%. The expected effect is reduced according to an intervention to intervene analysis; we expect a GP participation rate at the CME-meetings of 40%. Uncorrected for clustering and repeated measures, a total sample size (N) of 5116 patients would be required (power of 99% and significance level of 0.05).

To accommodate the stepped wedge clustering effect N has to be multiplied by the design effect (DE) [57]: N_*sw*_ = DE*N, where$$ DE=\frac{1+\rho \left(ktn+bn-1\right)}{1+\rho \left(\frac{1}{2}ktn+bn-1\right)}\cdotp \frac{3\left(1-\rho \right)}{2t\left(k-\frac{1}{k}\right)} $$

Here, *ρ* is the intra-cluster correlation, *k* is the number of steps, *n* is the average cluster size, *b* is the number of baseline measurements and *t* is the number of measurements after each step. In our study *k* = 8, *b* = *t* = 1. Furthermore, we assume that *ρ* = 0.05, as it is a typical value for intra-cluster correlation for clinical outcomes in primary care [58]. The cluster size can be expressed as *n* = *N*_sw_ / *c*, where *c* is the number of clusters. The number of clusters is known in advance (*c* = 8) and the question is how many subjects per cluster should be sampled to provide the power required. Using the equations described above, this cluster size is estimated as *n* = 200 through an iterative procedure. Therefore, the total sample required (*N*_sw_) is 1,653. In Central Denmark Region, 5,400 new cancer patients are expected in an 8-month period. We assumed that 40% [59] of those (2,200) will be referred from general practice to a cancer fast-track pathway. With an assumed PPV for diagnosing cancer in fast-track pathway on 20% and an assumed GP response rate on 70%, we expect to receive one-page forms with information on primary care intervals on 7,700 patients. Thus, it is considered that the study has ample strength—also in relation to three stratified subgroups of GPs and adjustment for multiple predictors.

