### Strengths and limitations of the study

With a detailed description of the CME elements, training process and context, we have tried to optimise the possibilities for an adaptation/replication in other settings.

The time frame of the present study did not afford us with the possibility to conduct an explorative study on the target group before the trial; instead, a full-scale CME was conducted in an external regional cancer steering group, and the findings were subsequently evaluated, discussed and approved.

Randomising individual GPs to the CME intervention was considered unfeasible as much of the effect would include GPs working together and discussing cancer diagnosis within practices and in the CME groups. Preventing GPs from participation was considered unethical since the CME was a part of the Danish Cancer Plan, and it was considered important that all patients could benefit from an improved clinical practice. A cluster randomised stepped wedge study was thus preferred. Using this design, we will be able to control for time trends by allowing contemporaneous comparisons across clusters at different time periods.

Designing a study in real life, however, raised some challenges with regard to controlling the intervention. A specific CME date was offered to all GPs, but they were free to decide whether they wanted to participate or not. The collected data will allow us to compare the three GP subgroups of each cluster at a baseline level to explore potential selection bias.

GP knowledge, attitude and self-assessed readiness to refer will be measured by online questionnaires before and after the CME to allow paired analyses to be performed. The GPs were informed in the invitation letter that the questionnaire attempted to measure activity related to cancer diagnosis in general practice. This could have influenced the responses.

By placing a pad with forms in each GP office and by sending regular reminders (every second week), we expect to collect prospective data, i.e. to obtain data before the GPs know whether the referred patient had cancer or not. In cases where the GP forgot to complete a form and had to be requested to do so, information bias can occur. Furthermore, lead time bias will be considered when reporting the 1-year survival. This outcome will be evaluated in close relation to potential change in cancer stage.

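### Non-attending GPs alone at their address can only fall in subgroup 3, so subgroups 2 and 3 differ in practice size by definition and comparisons between them need restriction to shared addresses

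*Protocol article*

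**What the plan says.** The Statistical analyses section plans analyses in the full GP population and in three subgroups. Subgroup 1 is the attenders. The non-attenders are divided into "2) GPs who did not participate in the CME, but had at least one colleague who participated, and 3) GPs who did not participate" and, with the rule that decides between the two, "had no colleagues who participated. A colleague is defined as a GP with the same clinic address as the respondent". The legend of Figure 2 repeats the split and describes the groups as strata.

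Under Strengths and limitations of the study, the article says that GPs were free to attend or not, and that the data will be used to "compare the three GP subgroups of each cluster at a baseline level to explore potential selection bias".

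Three further statements bear on this. Table 3 notes that "GPs can choose to work in solo practices or in group practices". The Setting section gives "417 GP clinics with 836 GPs". The Register data section lists "the number of GPs in each general practice" among the items held in the provider number registry, together with GP names and addresses.

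**The concern.** The split is meant to separate non-attenders by contact with an attending colleague, but it also sorts them by how many colleagues they have. A GP with nobody else at the address has no colleague who could attend, so on non-attendance that GP is placed in subgroup 3 with certainty. A GP at a large address enters subgroup 3 only if everyone there stays away. Subgroup 2 is therefore weighted towards large addresses and subgroup 3 towards solo and small ones, whatever the GPs' reasons for attending.

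Two readings are exposed. First, a baseline difference between subgroups 2 and 3, or between either of them and subgroup 1, may reflect practice size and whatever goes with it rather than self-selection. Second, if a CME effect appeared in subgroup 2 but not in subgroup 3, it could be spread from colleagues or simply a different response in group practices. The data as grouped could not tell these apart.

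**Working it through.** **Inputs from the article.** Clinics 417 and GPs 836 (Setting), so the mean is 836/417 = 2.00 GPs per clinic. Expected attendance: "we expect a GP participation rate at the CME-meetings of 40" per cent (Power calculation). Solo practices exist (Table 3), but their share is not given. The article states no figure for the make-up of the subgroups, so there is none to reproduce.

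**Assumption for the first step.** Each GP attends with probability p = 0.40, independently of colleagues. This is deliberately a world without self-selection.

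**Formulas.** For a GP at an address with m GPs:
- P(subgroup 1) = p = 0.40, whatever m
- P(subgroup 2) = (1 − p)(1 − (1 − p)^(m−1)) = 0.6 × (1 − 0.6^(m−1))
- P(subgroup 3) = (1 − p)^m = 0.6^m

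| GPs at address | Subgroup 2 | Subgroup 3 |
|---|---|---|
| 1 | 0.6 × (1 − 1) = 0 | 0.60 |
| 2 | 0.6 × (1 − 0.6) = 0.24 | 0.36 |
| 3 | 0.6 × (1 − 0.36) = 0.38 | 0.22 |
| 4 | 0.6 × (1 − 0.216) = 0.47 | 0.13 |
| 6 | 0.6 × (1 − 0.078) = 0.55 | 0.05 |

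**From probabilities to group make-up.** This needs a clinic-size distribution, which the article does not give. Assumption: a share s of the 417 clinics is solo. The rest have 2 to 8 GPs with geometrically changing weights, chosen so that the overall mean stays at 2.00, and each clinic counts as one address. Means are per GP.

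| Solo clinics (assumed) | Mean size, subgroup 1 | Mean size, subgroup 2 | Mean size, subgroup 3 | Solo GPs in subgroup 3 |
|---|---|---|---|---|
| 10% | 2.12 | 2.28 | 2.01 | 9% |
| 30% | 2.44 | 2.99 | 1.98 | 27% |
| 60% | 3.29 | 4.74 | 1.78 | 61% |

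Solo GPs are 0% of subgroup 2 in every row.

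**Sensitivity to clustering of attendance.** With attendance correlated within practice (beta-binomial, assumed correlation 0.3), mean size over solo shares of 10% to 60% is 2.3 to 4.8 in subgroup 2 against 2.1 to 2.5 in subgroup 3. Solo GPs are then 7% to 47% of subgroup 3. The gap is smaller but remains.

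**Attenders against all non-attenders.** Pooling subgroups 2 and 3 removes the artefact. In the 30% row, the pooled mean is (228 × 2.99 + 274 × 1.98)/(228 + 274) = 2.44, the same as in subgroup 1.

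**Is dropping solo GPs enough?** Not quite. In the 10% row, the solo non-attenders number 417 × 0.10 × 0.6 = 25 of the 292 in subgroup 3. Without them its mean size is 2.10 against 2.28 in subgroup 2. In the 60% row they number 417 × 0.60 × 0.6 = 150 of 245, and the means become 3.01 against 4.74. Restriction removes the group with no counterpart. Stratification or adjustment by number of GPs has to deal with the rest.

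**The case against.** The strongest reply is that little of what the article actually states is damaged, and much of that reply stands.

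- A reader might infer that the plan will read a subgroup 2 versus 3 difference as spillover. The article states no such contrast. It says only that analyses will be done in the three subgroups. The inference is natural, because the discussion expects much of the effect to arise from GPs in a practice talking to each other, but it remains an inference.
- A reader might infer that the subgroup effects themselves are biased by practice size. They are not, by this route. Each comes from periods before and after the CME across clusters with staggered dates, and practice size is essentially fixed over eight months.
- A reader might infer that the selection-bias check must give a false answer. It is described as exploratory, with no decision rule, and a difference in practice size could be recognised as such. Attenders against all non-attenders is untouched by the definition.
- The size of the imbalance rests on assumed clinic mixes and may be small (2.3 against 2.0 GPs). Nothing in the article links practice size to either primary outcome or to response to the CME, so no bias in an outcome can be computed.
- Colleagues are defined by address. A GP with an own provider number at a shared address can be in subgroup 2, so the point is exact only for a GP alone at an address.

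It is also said that adjustment may deal with this. The Power calculation section does foresee adjusting for several predictors, without naming them, and the details may be in an analysis plan that is not shown. But the grouping rule is fixed in the article, and no adjustment can supply GPs alone at an address to subgroup 2. For them the comparison would be pure extrapolation. The three-group baseline comparison is also stated in the article, with no pooling of non-attenders.

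**Conclusion.** The point holds in a limited form. By the article's own definition, subgroups 2 and 3 differ in practice size even when attendance is random. This contaminates the stated three-group baseline look at selection, and it would confound any comparison of CME effects between subgroups 2 and 3. The direction of the imbalance is certain as long as some clinics are solo and attendance is roughly random. Its amount is not known: across assumed solo shares of 10% to 60%, it runs from 2.3 against 2.0 to 4.7 against 1.8 GPs per address.

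The documents do not support the stronger conclusion that the subgroup analyses are invalid or that the trial's main result is at risk. The intention-to-intervene analysis and the sample size do not depend on this split. It is a worthwhile, low-cost improvement to supplementary analyses.

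**What to change.** In the Statistical analyses section:

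1. Report non-attending GPs with no other GP at the address as a separate group.
2. Compare subgroups 2 and 3, at baseline or for the CME effect, only at addresses with two or more GPs, stratified by or adjusted for the number of GPs at the address.
3. Base the selection-bias check on attenders against all non-attenders combined.

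The count should be made by address, to match the definition of a colleague. The provider number registry holds both addresses and GPs per practice, so no new data source is needed. The article reports that register data had not yet been obtained.

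The cost is a smaller subgroup 3 in that one comparison. Under the assumptions above it falls from 292 to 267 GPs if 10% of clinics are solo, and from 245 to 95 if 60% are.
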